## Abstract

Heritable human genome editing (HHGE) presents new possibilities for the prevention of genetic diseases but also raises ethical and societal questions. While international surveys have explored public attitudes, particularly in high-income countries, there is a lack of large-scale empirical data from the Global South. In South Africa, previous work used deliberative public engagement to examine public perspectives. The present study aims to complement this by capturing public opinion through a cross-sectional survey, enabling direct comparison with deliberative findings. This study will recruit 400 adult participants residing in South Africa using targeted Facebook advertisements. A two-phase sampling process will be employed: initial screening for demographic information, followed by stratified sampling to ensure a representative South African population. The opinion survey consists of 19 HHGE scenarios, each explored through private and public moral lenses. Additionally, participants will indicate their interpretation of ‘safe and effective’ genome editing. Quantitative data will be analysed using descriptive statistics, chi-square tests, and logistic regression. Qualitative responses will undergo thematic analysis using both manual coding and generative AI tools under human oversight. The study includes two stages of informed consent and ensures data confidentiality through strict data handling protocols. Results will be disseminated in peer-reviewed journals and policy forums. The study will also generate a secondary dataset for evaluating AI-assisted qualitative analysis, to be conducted under separate ethical clearance.

## Background

Heritable human genome editing (HHGE) is a ground-breaking biotechnology that enables the modification of human DNA at the embryonic stage, with changes passed down to future generations. This technology holds the potential to prevent serious genetic disorders and reduce disease burdens, but it also raises urgent ethical, legal, and societal concerns [1]. Public opinion can affect the adoption of gene editing technologies [2]. As countries move toward establishing governance frameworks for HHGE, understanding public attitudes has become a critical component of responsible policy development [2].

Internationally, studies on public opinion elucidate the contestations around HHGE application. Participants were concerned about who HHGE will affect and for what it will be used [1]. As such, these opinions varied based on morality, risk perception, and benefit perception [2,3], as well as whether HHGE would be used specifically to prevent severe genetic diseases, protect against infectious disease, or used for enhancements [3,4]. These surveys revealed broad support for therapeutic applications of HHGE, particularly those aimed at preventing serious genetic diseases [3,4] In contrast, there is significantly less support for non-therapeutic enhancements, such as modifications related to intelligence or appearance [3–5]. These trends suggest that the public tends to support HHGE when framed as a tool for alleviating suffering but resists applications seen as enhancing traits beyond species-typical norms.

While these findings are informative, they largely reflect the views of populations in high-income countries, such as the Netherlands [1,4], Canada, the US, Austria, Germany and Italy [2], Japan [3] and the United States of America [5]. There is a notable absence of large-scale public opinion data from the Global South, particularly from African countries, where the socio-economic context and health priorities may shape public views differently [6]. In low- to middle-income countries, for example, support for genome editing to enhance immunity to infectious diseases has been higher, aligning with local disease burdens [6]. Jibrilla et al. [7] provide one pertinent example of a study on public opinion in Nigeria, although they do not focus on HHGE. Their findings show that there is generally support for gene editing, particularly to prevent or reduce the risk of severe diseases [7]. It is also important to note that none of the existing studies frame the policy scenarios in light of the recent pandemic, i.e. the COVID-19 pandemic, to establish whether the aftermath of this may affect public sentiment towards using HHGE to prevent possible future pandemics caused by emerging pathogens.

In South Africa, the earliest empirical studies of public opinion on HHGE were conducted by [name] et al. [8,9] through deliberative public engagement. These studies found strong public support for the use of HHGE to prevent severe heritable diseases and enhance immunity to major infectious diseases, such as tuberculosis (TB) and HIV/AIDS, which may correlate to the disease burden observed in South Africa. However, support declined markedly for editing aimed at less serious conditions, disabilities, or non-medical traits such as eye colour or intelligence. Importantly, these findings were based on small groups that were informed about HHGE, as per [name] et al.’s [8] protocol, and deliberated their views on a facilitated platform. Thus, these views may not reflect broader public sentiment where people are not intentionally informed about HHGE nor have the opportunity to deliberate with individuals who have different perspectives.

The current study addresses this gap by conducting a large-scale, cross-sectional survey of public opinion on HHGE among South Africans. By using the same 15 scenarios from the [name] et al. deliberative engagement study – plus five additional or amended scenarios exploring perceptions linked to pandemic preparedness and to atypical species’ characteristics – this survey enables direct comparison between informed and uninformed views. In doing so, it contributes both nationally and globally to the understanding of public attitudes toward HHGE applications, while also highlighting how local socio-cultural and health factors shape perspectives on emerging biotechnologies.

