## Research objectives

The study is guided by the following research objectives:To determine the level of public support for potential HHGE applications in the future aimed at specific health scenarios, including:
Editing to correct genetic errors to prevent categories of genetic conditions, ranging in the severity of their health-related symptoms or complications and/or sociocultural implications in the South African setting;Editing to confer immunity against categories of infectious diseases which range in the severity of their health-related symptoms or complications, with a sub-focus on editing to prepare a population for hypothetical pandemic scenarios;Editing to influence non-health-related traits, also referred to as enhancement.To examine demographic variations in public opinion, by analysing responses according to population group, age, sex, and education level.To compare:
Spontaneous public opinion captured in this study with deliberative public views reported by [name] et al. [9].Private moral choices (what individuals would choose for their own child) with public moral views (what individuals think the law should allow for society at large).To assess public perspectives on the temporal focus of science policy, specifically whether it should focus solely on what is currently safe and effective or also consider future scientific developments that may become safe and effective.To identify public interpretations of what constitutes ‘safe and effective’ HHGE and examine how these interpretations influence participants’ support for various applications of genome editing.To contribute to the global literature on HHGE, by:
Identifying alignments or divergences between South African public opinion and trends observed in high-income countries.Exploring the influence of local health challenges and socio-cultural contexts on attitudes toward HHGE.

By achieving these objectives, the study will provide robust empirical evidence to inform policy, ethical debates, and governance frameworks on genome editing in South Africa and comparable settings.

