### Participant recruitment and data collection processes

Participants will be recruited using targeted Facebook advertisements aimed at South African residents aged 18 years and older. Facebook was selected as the primary recruitment platform due to its extensive reach across demographic groups in South Africa. As of January 2024, approximately 74.7% of South Africans aged 16 to 65 reported using the internet, and of these individuals, 88.4% reported using Facebook at least once per month [10]. Therefore, 66% of the population within this age group likely use Facebook. This makes Facebook the social media platform with the highest advertisement reach in the country, rendering it both practical and cost-effective for large-scale recruitment.

Recruitment will occur in two phases. In the first phase, individuals will be directed via Facebook ads to the study’s dedicated Facebook page, where they can access a link to the screening questionnaire hosted on SurveyMonkey. Upon accessing the survey platform, potential participants will be presented with an informed consent form detailing the purpose of the study, data use, the voluntary nature of participation, and compensation procedures. Only those who consent on this online form via writing/ticking will proceed to complete the screening questions, collecting their demographic data, including age, sex, population group, educational attainment, and religious affiliation, along with an email address. These data will be used for stratified selection to ensure the final sample is demographically representative of the South African adult population.

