## Discussion

The prospective study based on this protocol offers a timely and necessary intervention into the emerging field of public engagement with HHGE, particularly within underrepresented contexts such as South Africa. By capturing the spontaneous, non-deliberative views of a demographically representative population sample, it responds to growing calls for more inclusive and locally grounded data on public attitudes toward genomic technologies.

For practice, the prospective study will provide empirical insights into how South Africans interpret core ethical concepts such as safety, effectiveness, and permissibility in the context of HHGE. These findings can assist clinicians, genetic counsellors, and science communicators in better understanding how laypeople perceive risk, choice, and therapeutic intention, enabling more responsive engagement and communication strategies in clinical and community settings.

For policy, the study will offer robust public opinion data that can inform governance frameworks for genome editing in South Africa. Unlike deliberative studies that rely on informed participants, this survey captures widespread public sentiment, including moral and cultural intuitions that may otherwise remain invisible in policymaking processes. The dual framing of private and public morality further enriches the data, offering insights into how individuals differentiate between personal autonomy and societal regulation. These perspectives are essential for ethical policy development, particularly in democratic societies seeking legitimacy through public consultation.

For scholarship, the study contributes to global literature by expanding the geographic and methodological scope of public opinion research on HHGE. It introduces an innovative comparative design that links deliberative and spontaneous viewpoints, and it pioneers the integration of generative AI tools in qualitative data analysis. This methodological contribution lays the groundwork for future research into the epistemological, ethical, and practical implications of AI-assisted qualitative methods in empirical bioethics.

Through its design and scope, the study supports a more inclusive, context-sensitive, and methodologically plural understanding of how emerging biotechnologies are received by the public, which is an essential step in fostering ethically sound and socially legitimate science policy.

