## Limitations

While the study is designed to maximise representativeness and rigour, several limitations must be acknowledged. There are three limitations that can be identified from the outset of the study: limitations in Facebook recruitment; the cross-sectional versus longitudinal nature of the study; and the use of GenAI in analyses.

First, the online nature of recruitment may exclude individuals without reliable internet access, particularly in rural or economically disadvantaged areas. This constitutes a limitation of the sampling approach. No supplementary recruitment strategies will be implemented beyond the online platform, and this limitation is acknowledged explicitly. Facebook advertising was selected as the primary recruitment method because it offers a cost-effective way to reach a national audience within the study’s resource constraints. Complementary recruitment strategies, particularly in rural areas, are not feasible due to the financial and logistical demands of travel, translation and gatekeeper permissions. We acknowledge that this may lead to under-representation of some groups and note this as a limitation and an avenue for future research. Nevertheless, recent national data suggest that as of January 2024, 66% of the population within the age group of 16 to 65 likely use Facebook [10]. While this figure may not capture all usage patterns, it suggests that Facebook provides extensive coverage of the general adult population, including a substantial proportion of users from diverse socioeconomic backgrounds. Given that the aim of this study is to explore public attitudes toward HHGE rather than to produce nationally representative estimates, recruitment through Facebook remains a reasonable and pragmatic approach.

Second, as a cross-sectional survey, the study captures views at a single point in time and does not account for how public attitudes may evolve through exposure to new information or public debate. The absence of a deliberative component means that changes in opinion arising from education, reflection, or dialogue are not measured within this study.

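### The survey-versus-deliberation contrast can describe a difference between two studies, but it cannot support the informed-versus-uninformed reading given in the Background

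*Protocol article*

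**What the plan says.** The Background of the protocol article states that, with the scenarios carried over from the earlier work, "this survey enables direct comparison between informed and uninformed views". The Abstract also describes the comparison with the deliberative findings as direct. Under Research objectives, the first part of the third objective (3a below) is to compare "Spontaneous public opinion captured in this study with deliberative public views reported by" the earlier study. The Sample size justification says that 400 respondents support this comparison, and the Discussion says of the study: "It introduces an innovative comparative design that links deliberative and spontaneous viewpoints".

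On the comparator, the Abstract says: "In South Africa, previous work used deliberative public engagement to examine public perspectives". The Background adds that "these findings were based on small groups that were informed about HHGE" and that the participants "deliberated their views on a facilitated platform".

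On the present study, the recruitment section says: "Participants will be recruited using targeted Facebook advertisements aimed at South African residents aged 18 years and older". Study design and the recruitment section describe a SurveyMonkey questionnaire reached by a personal link. The sample of 400 is stratified, with weighting where minority groups are oversampled, to match the national adult population.

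Limitations names three topics: Facebook recruitment, the cross-sectional design and the use of generative AI. Under the second it says that "changes in opinion arising from education, reflection, or dialogue are not measured within this study".

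**The concern.** Asking the same questions in two studies does not make the respondents, or the conditions under which they answered, comparable. The Background's wording credits a single factor, being informed, for a contrast in which several factors move at once. Even the intended factor is a bundle, because the earlier participants were both informed and engaged in group deliberation; neither could be isolated from the other even if the samples matched perfectly.

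At stake is what Objective 3a may conclude. The article says that its objectives will yield evidence for policy. A gap that arises from who was asked, how they answered or when could reach policymakers as a finding about informed opinion. The private-versus-public comparison and the estimates of support within the survey are not affected.

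**Working it through.** **1. The two sides of the contrast, from the document itself**

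| Feature | Earlier study | This survey | Basis |
|---|---|---|---|
| Information | Informed | Optional introductory videos only | Background; Pre-survey educational materials |
| Deliberation | Yes, facilitated | None | Background; Limitations |
| Setting | Small groups | Individuals | Background; recruitment section |
| Mode | Facilitated platform | Self-completed online questionnaire | Background; Study design |
| Time | Earlier, dates not given | Prospective | Abstract; Discussion |
| Recruitment | Not described | Facebook advertisements | Recruitment section |
| Composition | Not described | Stratified to national adults | Stratified sampling section |

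The first five rows differ on the document's own account. The last two cannot be compared from the document. Respondents are not randomised between conditions, and nobody is measured before and after being informed, so the first five differences cannot be separated.

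**2. Which scenarios are common to both studies**

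Study design gives 19 scenarios, of which 15 correspond to the earlier study and five are new or amended. Since 15 + 5 = 20, one scenario appears to be counted twice. The likely candidate is the COVID-19 item, which Survey instrument says was turned into four pandemic questions. On that reading the unchanged set is 19 - 5 = 14. This is an inference for the authors to confirm.

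**3. The plan's sample-size figure**

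n = z² × 0.25 / d² = 1.96² × 0.25 / 0.05² = 384.15, rounded up to 385. The stated figure reproduces. At n = 400 the margin is 1.96 × √(0.25/400) = 0.049, or ±4.9 points. This formula concerns the precision of one proportion in one sample. It does not address a two-study comparison.

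**4. What 400 gives for the comparison (assumed comparator size)**

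The earlier study's size is not given. With p = 0.5, simple random samples and assumed comparator size m, the 95% half-width of the difference is 1.96 × √(0.25/400 + 0.25/m):

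- m = 20: 22.5 points
- m = 30: 18.6 points
- m = 50: 14.7 points
- m = 100: 11.0 points

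The comparator term dominates. With m = 30 and an unlimited survey sample, the half-width would still be 1.96 × √(0.25/30) = 17.9 points. Correlated answers within deliberating groups, and survey weights, would probably widen these figures. A larger survey would not remove confounding either.

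**5. Illustration of composition alone (all inputs assumed)**

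Spurious difference = gap in support between subgroups × difference in subgroup share.

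- 20 points × 0.15 = 3 points
- 20 points × 0.30 = 6 points
- 20 points × 0.45 = 9 points
- Wider range: 10 × 0.10 = 1 point, up to 30 × 0.50 = 15 points

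The document supplies neither input nor a direction. The calculation shows the mechanism only.

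**The case against.** The strongest reply is that Objective 3a is worded descriptively. It compares spontaneous with deliberative views and states no causal effect. The Abstract speaks of complementing earlier work, and the Discussion of linking two kinds of viewpoint. This stands: the article does not plan to isolate an effect of information. What remains is the Background sentence, which claims a property that the design does not have.

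Four further readings are tempting and are not supported.

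- **That recruitment and composition are known to differ.** The article does not describe either for the earlier study, nor whether its participants were paid. What can be said is that comparability is not shown.
- **That a long time gap is established.** The comparator is earlier, but no dates are given. It already carried a COVID-19 scenario, so it was not a pre-pandemic study.
- **That Limitations contradicts the Background.** Its sentence concerns change in opinion measured inside this survey. A comparison of levels between two studies is consistent with it. The sentence is a partial disclosure that is not carried over to Objective 3a.
- **That a bias of about 6 points has been demonstrated.** That figure rests wholly on assumed inputs and, for comparator sizes of 20 to 100, would lie inside the sampling half-widths above.

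It is also fair that adjustment for a secondary comparison may be left to an analysis plan or full protocol not shown here. Its absence from the article is therefore not the fault. The fault is the interpretation that the article does state.

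**Conclusion.** The point holds in a limited form. Objective 3a can describe a difference between two studies on common scenarios. It cannot support a reading as informed versus uninformed views, because information, deliberation, setting, mode and time change together and comparability of the samples is not shown. The three stated limitations do not cover this.

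No figure in the article is wrong on this point, and the 385 reproduces. The size of any distortion cannot be derived from the documents. The conclusion rests on the article's own account of the two studies and on no assumed number. It would stand even if no respondent watched the optional videos; any who do watch make the uninformed label less exact still.

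**What to change.** 1. In the Background, and in the Abstract where the comparison is also called direct, describe it as a descriptive between-study comparison. Add to Limitations that differences cannot be attributed to information or deliberation, because setting, mode and time also differ and the samples are not shown to be comparable.
2. Restrict Objective 3a to the scenarios left unchanged from the earlier study, and state how many there are.
3. If the earlier panel's demographic mix can be obtained, report beside the unadjusted comparison one in which survey respondents are weighted to that mix. Use only the few margins that a small panel can support, since cross-classifying several variables would leave sparse or empty cells. The earlier instrument came from the same principal investigator, so the mix may be obtainable, but the article does not say so. If it is not, items 1 and 2 suffice.

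The cost is changed wording, one extra set of weights, a weaker headline claim and a wider interval on the weighted comparison. Weighting removes only measured differences in composition; it does nothing for mode or time, so the limitation is needed either way. No new data collection is required.

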## Research objectives

The study is guided by the following research objectives:To determine the level of public support for potential HHGE applications in the future aimed at specific health scenarios, including:
Editing to correct genetic errors to prevent categories of genetic conditions, ranging in the severity of their health-related symptoms or complications and/or sociocultural implications in the South African setting;Editing to confer immunity against categories of infectious diseases which range in the severity of their health-related symptoms or complications, with a sub-focus on editing to prepare a population for hypothetical pandemic scenarios;Editing to influence non-health-related traits, also referred to as enhancement.To examine demographic variations in public opinion, by analysing responses according to population group, age, sex, and education level.To compare:
Spontaneous public opinion captured in this study with deliberative public views reported by [name] et al. [9].Private moral choices (what individuals would choose for their own child) with public moral views (what individuals think the law should allow for society at large).To assess public perspectives on the temporal focus of science policy, specifically whether it should focus solely on what is currently safe and effective or also consider future scientific developments that may become safe and effective.To identify public interpretations of what constitutes ‘safe and effective’ HHGE and examine how these interpretations influence participants’ support for various applications of genome editing.To contribute to the global literature on HHGE, by:
Identifying alignments or divergences between South African public opinion and trends observed in high-income countries.Exploring the influence of local health challenges and socio-cultural contexts on attitudes toward HHGE.

By achieving these objectives, the study will provide robust empirical evidence to inform policy, ethical debates, and governance frameworks on genome editing in South Africa and comparable settings.

